#### Missing data

An intention-to-treat approach (ITT) will be used in the main statistical analyses, which will include all randomized participants. The ITT analysis aims to estimate the population’s average causal effect by considering the randomised allocation regardless of whether the participants in each group complied or not with their allocation condition [68]. A complier average causal effect (CACE) will also be used to estimate the local average causal effect within the compliers [68]. ‘Compliers’ will be considered those participants who pointed at least 17 points in the adherence questionnaire (EARS-Br) [49].

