**Fig. 3 Fig3:**
[figure not shown]
Adaptation of Proctor’s conceptual model of implementation research

The primary implementation outcomes will be cost-effectiveness, adoption, and acceptability (satisfaction using a numerical scale from 0 to 100). Primary and secondary implementation outcomes are described below and summarized in Table 1.*Acceptability* will be analysed from the perspective of the organisation through a focus group, from the perspective of end-users through an individual qualitative interview about satisfaction with the intervention, and by a numerical scale from 0 to 100 on how satisfied they were in participating in the intervention. The acceptability of the implementation will also be evaluated by the Acceptability of Intervention Measure (AIM) [47] in organisations and end-users. The AIM has four questions with a Likert scale from 1 (completely disagree) to 5 (completely agree), and the mean of the score will be used (1 to 5). Higher scores indicate greater acceptability [47].*Appropriateness* will be analysed from the end-users’ perspective regarding the perception of the appropriateness of each component of the *EducaDor* programme about their health condition through an adapted questionnaire [48]. This questionnaire will assess the degree to which participants agree with a series of statements about the intervention, on a Likert scale from 1 (totally disagree) to 4 (totally agree). The appropriateness of the implementation will also be evaluated by the Intervention Appropriateness Measure (IAM) [47] in the organisation and end-users. The IAM score is the same as the AIM.*Feasibility* will be evaluated from the perspective of the organisation and individual providers through a focus group, and the Feasibility of Intervention Measure (FIM) [47] will be used in participants, organisations and individual providers. The FIM score is the same as the AIM and AIM.*Adoption* will be analysed by the percentage of acceptance of public health users to participate in the *EducaDor* programme referred from primary healthcare. We will contact by telephone those public health users who refuse to participate by inviting them to an individual qualitative interview to identify barriers to engagement in the *EducaDor* programme.*Fidelity* will be evaluated by an independent pain specialist ([name]), who will randomly select 10% of the recorded meetings and evaluate the intervention providers in relation to the fidelity of the intervention manuals with the content and quality of the meetings in a qualitative individual interview.The adherence of participants with the *EducaDor* programme will be measured by the frequency rate in synchronous meetings; self-rated performance of proposed homework on a numerical scale from 0 to 10 during the intervention period; and by exercise adherence scale (EARS-Br) [49].*Penetration* will be analysed descriptively from the rate of public health users referred from each primary healthcare unit.*Sustainability* will be evaluated by a focus group with public health managers after the presentation of the results of the study to discuss the maintenance of the *EducaDor* programme, and by a response rate of synchronous group users and reasons for discontinuity of the programme through an individual qualitative interview.*Costs* will be estimated from the SUS and societal perspectives in a time horizon of 6 months. The SUS costs will include the intervention costs and healthcare utilization costs covered by SUS. The intervention costs will be determined by preparation, video recording, development and editing, maintenance and support technology costs, monitoring data costs and staff, training health professionals and project management costs, number and duration of phone calls and the number of text messages sent to participants. The e-book and asynchronous intervention costs will be diluted in 10 years. The healthcare utilization costs covered by SUS will include prescribed drugs, medical consultations, physiotherapy-based care, visits to specialists, diagnostic exams, emergency services and hospitalisation. The societal costs will include the SUS costs, private healthcare costs, patient costs (out-of-pocket expenses with unprescribed drugs, complementary costs, and transportation costs), and lost productivity costs (related to absenteeism). The quantities of resource utilization will be identified by the participants in a self-rated diary cost that will be provided at baseline and an assessor will collect this information by telephone every 3 months. The healthcare utilization costs covered by SUS will be valued using the Brazilian standard costs [50]. Patient costs will be valued using the out-of-pocket expenses reported by patients. Private transportation will be valued by the price of Brazilian gasoline per kilometre and public transportation by the reference price of Guarapuava city. The lost productivity costs will be estimated from the hours of absenteeism to work (paid and unpaid) through a questionnaire, and evaluated according to the Human Capital Approach and will be valued using gender-specific price weights [50].

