
**Table 1 Tab1:** Implementation outcomes

**Outcomes**	**Level of analysis**	**Indicators**		**Data Collection Tool**		**Time of data collection**
**Acceptability**	Organisation	Acceptability of the implementation		Qualitative interview and Acceptability of Intervention Measure (AIM)		Post-implementation
	Participants	Satisfaction with the intervention		Qualitative interview and 0 to 100 points scale and AIM		Post-implementation
**Appropriateness**	Participants	Are the components of the online pain science education programme appropriate for the health condition?		Qualitative interview, Intervention Appropriateness Measure (IAM) and an adapted questionnaire used by Liao et al. (2020)		Post-implementation
	Organisation	If intervention is appropriate for the public health condition		Intervention Appropriateness Measure (IAM)		Post-implementation
**Feasibility**	Participants	Feasibility of the intervention		Feasibility of Intervention Measure (FIM)		Post-implementation
	Organisation	Feasibility of the implementation		Qualitative interview and FIM		Post-implementation
	Individual providers	Feasibility of the implementation		Qualitative interview and FIM		Post-implementation
**Adoption**	Participants	Enrolled participants being contacted		Own domain database		During implementation
		Burden (reasons for not taking part)		Qualitative interview during triage		Pre-baseline
**Fidelity**	Creator of the intervention	10% of taped sessions of the intervention group were randomly selected and reviewed by an expert panel, against the full detailed intervention manuals for adherence and quality		Qualitative interview		Post-implementation
	Participants	Number of participants that adhered to the intervention		Frequency during intervention		During implementation
		Self-rated performing the proposed activities at home for 10 weeks and the 6-month of follow-up		Adherence to the proposed homework (0 to 10 points scale); and the exercise adherence scale (EARS-Br)		Post-implementation
**Penetration**	Organisation	Which primary healthcare units referred users with musculoskeletal pain for intervention?		Health regulation data and/or digital health record		During and post-implementation
**Sustainability**	Organisation	Do you think this project will be sustainable over time?		Qualitative interview		Post-implementation
	Participants	Indicator of drop in the response rate of the synchronous group		Own domain database		During implementation

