#### Physiotherapy-based care

All participants will receive physiotherapy-based care in one of the five physiotherapy centres accredited to SUS, according to the scheduling availability of the services. The physiotherapy-based care consists of 10 sessions, mainly based on exercises and electrophysical agents. Patients will be treated in an outpatient physiotherapy centre by independent therapists to minimize the possible preference bias of therapists.

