To evaluate the robustness of the results, two exploratory sensitivity analyses will be performed. The first sensitivity analysis will be performed by excluding the total costs of the e-book and the asynchronous video development and editing. The second sensitivity analysis will be performed considering only patients with more than 75% of adoption of the intervention. The economic evaluation will be conducted at RStudio.

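### The supplementary CACE defines compliers by a home-activity adherence score reachable in every arm, so it does not estimate the effect of receiving the randomised delivery mode; the 75% adoption subset has no patient-level definition

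*Protocol article*

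**What the plan says.** All places are in the protocol article.

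- **Missing data.** The main analyses are ITT over all randomised participants, "regardless of whether the participants in each group complied or not with their allocation condition". The section then adds: "A complier average causal effect (CACE) will also be used to estimate the local average causal effect within the compliers". Compliers "will be considered those participants who pointed at least 17 points in the adherence questionnaire (EARS-Br". This one rule serves all three arms.
- **Implementation outcomes, adherence text.** Adherence "will be measured by the frequency rate in synchronous meetings", by a 0 to 10 self-rating of homework, "and by exercise adherence scale (EARS-Br". Table 1 places the homework rating and EARS-Br under the indicator "Self-rated performing the proposed activities at home for 10 weeks and the 6-month of follow-up".
- **Implementation outcomes, adoption text.** Adoption is the percentage of users referred from primary care who accept to take part in the programme.
- **EducaDor programme, Strategies for engagement and Physiotherapy-based care.** The e-book with its weekly activities, the weekly homework messages and the physiotherapy go to every arm. The physiotherapy "consists of 10 sessions, mainly based on exercises and electrophysical agents". Only the synchronous arm has the ten weekly meetings, and only the video arm has the ten weekly videos. The video and e-book arms each begin with one introductory synchronous meeting.
- **Economic evaluation.** The second of two exploratory sensitivity analyses is done "considering only patients with more than 75% of adoption of the intervention".

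**The concern.** The trial randomises the mode of delivery, and the ITT sentence describes compliance as compliance with the allocated condition. A CACE in that sense needs a variable that records whether the allocated mode was received and that allocation strongly shifts. EARS-Br of 17 or more is a different thing: a participant can reach it in any arm without attending a weekly meeting or watching a video, or can attend everything and fall short of it.

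Two problems follow. Meetings or videos can change pain without changing the score, so the exclusion restriction fails. The between-arm difference in the share reaching 17 may also be small, which makes the estimate unstable. A reader of the results would take the CACE as the effect of complying with the allocated mode, which it would not be.

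In the economic check, no patient has an adoption percentage under the protocol's own definition. If adherence is meant, attendance at a weekly series can be counted only in the synchronous arm, and no viewing measure is named for the videos. Cost-effectiveness is a primary implementation outcome, so a robustness check on it should be interpretable.

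**Working it through.** **No figure to reproduce.** The protocol gives no compliance rates and no CACE value. The cut-off of 17 comes from a cited source and cannot be checked here. All compliance rates and ITT differences below are assumptions, shown over a range.

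**1. What the score can separate.** What was randomised is the ten meetings, the ten videos, or neither. What EARS-Br rates is performance of activities at home. The material and prompts for those activities are the same in all arms. The rule therefore measures something available everywhere, and attendance, which is collected, does not enter it.

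**2. Instrumental-variable arithmetic.** CACE = ITT / (pA - pB), where p is the share classed as compliers in each arm.

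Inputs for the standard error are the SD of 2.3, the 105 per arm and the 30% loss from Sample size estimation. With 105 x 0.70 = 73.5 per arm, SE(ITT) = 2.3 x sqrt(2/73.5) = 0.38. This ignores clustering and repeated measures and treats pA and pB as known, so SE(CACE) = 0.38 / (pA - pB), computed before rounding.

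| pA vs pB (assumed) | CACE if ITT = -0.5 | CACE if ITT = -1.0 | SE |
|---|---|---|---|
| 60% vs 0% | -0.83 | -1.67 | 0.63 |
| 60% vs 30% | -1.67 | -3.33 | 1.26 |
| 60% vs 40% | -2.5 | -5.0 | 1.90 |
| 60% vs 50% | -5.0 | -10.0 | 3.79 |
| 60% vs 60% | undefined | undefined | undefined |

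The -1.0 column uses the protocol's hypothesised difference. The first row is what receipt of a weekly series that the comparator lacks would give. The lower rows are what a score reachable in both arms could give.

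**3. Simulation.** 2,000,000 patients per scenario. The true effect of receipt on pain is -1.0. Receipt is possible in one arm only (63% to 64%). Both receipt and an EARS-type threshold depend on prognosis, and the threshold has no effect of its own on pain.

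- Instrumental variable on receipt: -0.99 to -1.01.
- Instrumental variable on the threshold: -2.44 when it is met by 76% vs 50%, -6.05 at 61% vs 50%, undefined at 50% vs 50%.
- Comparison of adherers only: -0.57, -0.51 and -0.41, against ITT values of -0.63 to -0.64. Part of the gap to -1.0 is dilution by adherers who did not receive the mode.
- True effect zero, adherers only: +0.08 and +0.20, which is selection alone.

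The last two lines apply to the economic subset, and also to the CACE if it were run as a plain comparison of compliers.

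**The case against.** The strongest reply has four parts.

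- **EARS-Br is relevant to EducaDor.** Home activities are central to a self-management programme, and Table 1 ties the score to them. This stands: a reader might infer that the score has nothing to do with the programme, and the documents do not support that. Nor does any section say that EARS-Br rates the physiotherapy sessions. But homework is common to all arms, so the score still does not identify receipt of the randomised mode.
- **Inflation is not shown.** A reader might infer that the CACE will be undefined or wildly inflated. The documents give no rates, and the synchronous sessions include work on the chapter activity, which could raise home performance in that arm. The protocol also names no estimator. So the size is open. The complier definition is nevertheless fixed in the protocol, and no choice of estimator turns it into a measure of receipt.
- **The arms are less separate than they look.** A reader might infer that the e-book arm has no synchronous contact and no video. In fact the e-book and video arms have an introductory meeting, and the e-book itself contains videos and podcasts. Only the weekly series are exclusive.
- **The 75% wording may be a slip for adherence.** Table 1 does list frequency during the intervention. That makes it a matter of clarification in part, but a subset chosen on adherence after randomisation remains a selected comparison.

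**Conclusion.** The point holds for two supplementary analyses. The CACE as defined cannot be read as the effect of complying with the allocated mode, because its complier variable is a home-activity score open to every arm. The 75% adoption subset is undefined per patient under the protocol's own use of the term, and any per-patient version conditions on post-randomisation behaviour.

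The size cannot be stated. Under assumed rates and an ITT of -0.5, the CACE runs from -0.83 (60% vs 0%) to -5 (60% vs 50%). That range shows sensitivity to the definition and is not a forecast.

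A reader might go further and doubt the main results. The documents do not support that: the main effectiveness and economic analyses are ITT and do not depend on either definition. The 75% analysis is labelled exploratory and does not itself claim to estimate the effect of receipt.

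**What to change.** - **Define receipt by the mode-specific component:** the number of the ten weekly meetings attended (already collected) and the number of the ten weekly videos viewed, asked in the weekly message that all groups already get.
- **Estimate two CACEs, with randomisation as instrument:** synchronous vs e-book, and video vs e-book. Restrict both to readers, because participants who cannot read or write are not randomised to the e-book arm. Synchronous vs video stays an ITT comparison.
- **Exposure:** use the number of sessions received, or any receipt, as the main definition. Use a 75% threshold only as a sensitivity analysis, with its exclusion assumption stated, since it treats someone with 7 of 10 sessions as having received nothing.
- **State the contrast exactly:** the e-book arm lacks the weekly series but has an introductory meeting and the e-book media.
- **Economic check:** replace the adoption subset with the same receipt-based CACE for costs and effects. State the exclusion assumption separately for costs, since items such as preparation and project management arise whether or not a participant attends.
- **Keep EARS-Br** as a descriptive adherence outcome.

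The cost is changed wording and one added message item. Self-reported viewing will bring some misclassification, and the CACE is less precise than ITT: at 60% vs 0% its SE is 1/0.60 = 1.67 times as large.

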#### Quantitative data analysis

For continuous variables, we will calculate statistics of central tendency and dispersion, such as means and, standard deviation. For categorical variables, we will describe frequencies and absolute numbers. Normality will be investigated by visual inspection of histograms. The baseline characteristics of the participants and implementation outcomes will be calculated using descriptive statistics. The differences between groups and the 95% confidence interval will be calculated using mixed models. The fixed effect term will be composed of dummy variables indicating groups, and follow-up time-points, that is, 10 weeks and 6 months after baseline, and the interaction terms composed of group and time. The estimates will be adjusted for any potential differences that might exist at the baseline. The random effect term will be composed of: (1) a correlated random intercept and slope varying the intercept for the five physiotherapy clusters and varying the slope for time points; and (2) a correlated random intercept and slope varying the intercept for repeated measurements within each cluster and varying the slope for time-points [69].

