#### Sample size estimation

The sample size was estimated by simulation [61, 62]. The sample size simulation was performed in four steps: (1) defining the sample size problem and outcomes; (2) defining, writing and running the sample size simulation algorithm; (3) estimating the possible outcomes derived from the simulations; (4) finding the optimal sample size.

In step 1, the sample size problem was developed considering the following objective: to estimate the minimum sample size required to comply with a maximal type I error (*α*) of 0.05 or 5% and a maximal type II error (*β*) of 0.20 or 20%. The input outcomes were: populational mean pain intensity (0–10) of 6.0 with a standard deviation (SD) of 2.3; a hypothesised minimal clinically important difference (MCID) in pain intensity between groups of -1.0 with an SD of 0.25 [63]; three groups; three repeated measurements (baseline, 10 weeks and 6 months); a correlation within the repeated measurements of 0.30 or 30% [64]; a minimum of 30 participants per cluster (five physiotherapy facilities); a correlation within clusters of 0.20 or 20% [65]; and a loss to follow-up of 30% [66].

In step 2, the simulation algorithm was defined and written in R language [67]. The input outcomes defined in step 1 were then included in the algorithm. Normal distributions were simulated using the input means and SDs set in step 1 as hyperparameters. The simulations were gathered running the distributions considering several possible sample sizes for one group ranging from 5 to 5000 in 32 steps (i.e., 5 to 50 by 5; 60 to 100 by 10; 150 to 500 by 50; 600 to 1000 by 100; and 2000 to 5000 by 1000), with 100 replications for each step, and repeating this procedure 10 times (i.e., 10 iterations), summing up 32,000 sample size simulations in total.

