In step 3, we estimated summary statistics for the simulated distributions in each of the 32 possible sample sizes, including the probability of type I error (*α*), type II error (*β*) and power (1-*β*). In step 4 we found the minimum sample size required to achieve the pre-defined type I error (*α* ≤ 0.05 or 5%), type II error (*β* ≤ 0.20 or 20%) and power (≥ 0.80 or 80%). At this moment the suggested minimum sample size was 80 participants per group. Then, corrections for loss to follow-up and correlations amongst the five clusters (physiotherapy facilities) and repeated measurements were applied [64, 65]. The sample size simulation suggested a minimum sample size of 105 participants per group, that is, 315 participants (105 in each treatment group) in total for this study.

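### As written, the pain model most naturally treats baseline as an outcome level; if the effect is then read from group × time, about 35% of the information is lost at the plan's own correlation of 0.30

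*Protocol article*

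**What the plan says.** The Effectiveness outcomes section makes current pain intensity on the 0–10 scale the primary effectiveness outcome, measured at baseline, 10 weeks and 6 months.

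The Quantitative data analysis section takes between-group differences from mixed models. The fixed part has dummies for group and for "follow-up time-points, that is, 10 weeks and 6 months after baseline, and the interaction terms composed of group and time". The next sentence reads "The estimates will be adjusted for any potential differences that might exist at the baseline". It names no variable and no form of adjustment. The section does not say which coefficient, or combination of coefficients, will be reported as the treatment effect.

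The Sample size estimation section lists as inputs "three repeated measurements (baseline, 10 weeks and 6 months); a correlation within the repeated measurements of 0.30". It therefore counts baseline as a repeated measurement alongside the two follow-ups.

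**The concern.** With an intercept, two dummies for the two follow-ups need a third time level as reference, and the only candidate is baseline. Baseline pain then sits in the outcome vector. With a freely estimated group term, each group × time coefficient is a between-group difference in change from baseline.

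A change-score contrast is efficient only when baseline and follow-up are strongly correlated. The plan assumes a weak correlation, 0.30. At that value, subtracting baseline adds more noise than it removes, so the contrast is less precise than one that ignores baseline altogether.

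The adjustment sentence does not settle the matter. It can be met simply by having a group main effect, and its wording links adjustment to differences that may turn up at baseline rather than prespecifying it for everyone. At stake are the width of the intervals and the power for the primary effectiveness outcome and for the secondary continuous outcomes analysed the same way.

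**Working it through.** **Inputs** (Sample size estimation section): "populational mean pain intensity (0–10) of 6.0 with a standard deviation (SD) of 2.3"; a difference "in pain intensity between groups of -1.0 with an SD of 0.25"; r = 0.30 between repeated measurements; 30% loss to follow-up; type I error 5%; "power (≥ 0.80 or 80"%). Sidedness is not stated, so I take two-sided.

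**The plan's own figure.** The section reports that "the suggested minimum sample size was 80 participants per group" before corrections. A two-sample comparison of single scores with difference 1.0 and SD 2.3 has power 78.5% at 80 per group and needs 84 per group for 80%. The simulation grid moves from 80 to 90 in this range, so 80 is reproduced to within about 2 points of power. It matches a comparison of follow-up scores alone. The step from 80 to 105 cannot be reproduced uniquely: 80 × 1.3 = 104 and 80 × (1 − 0.30²)/0.7 = 104 both come close, 80/0.7 = 114.3 does not, and no formula is given.

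**Which model the terms describe.** Three groups, two time dummies and their interactions give 1 + 2 + 2 + 4 = 9 fixed-effect columns.
- Three time levels × three groups give 9 cells, so all 9 columns are estimable.
- Two follow-up levels × three groups give 6 cells. The 9 columns then have rank 6, and the terms cannot all be estimated as written.

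The listed terms therefore fit baseline as an outcome level.

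**Whether the adjustment sentence changes this.** Suppose baseline pain is added as a main-effect covariate while baseline stays in the outcome vector. The covariate is constant within a participant, so it cannot move a within-participant contrast. On simulated complete data (80 per arm, r = 0.30), group × time equalled the raw change-score difference with and without it. Adjustment helps only if baseline leaves the outcome vector, or if baseline means are constrained to be equal.

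**Variance per participant, in units of σ²** (equal variance over time):
- Change: 2(1 − r) = 1.40
- Follow-up only: 1.00
- Baseline as covariate: 1 − r² = 0.91

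Information lost by change against covariate adjustment: 1 − 0.91/1.40 = 35%. Intervals are wider by √(1.40/0.91) = 1.24, or 24%.

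**Sensitivity to r:**

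| r | Change | Covariate | Information lost |
|---|---|---|---|
| 0.2 | 1.60 | 0.96 | 40% |
| 0.3 | 1.40 | 0.91 | 35% |
| 0.5 | 1.00 | 0.75 | 25% |
| 0.7 | 0.60 | 0.51 | 15% |

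Change is worse than ignoring baseline only when r is below 0.5.

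**Power.** SE = 2.3 × √(2v/n), where v is the variance factor; power = Φ(1.0/SE − 1.96); pairwise, no clustering, no multiplicity adjustment:

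| n per group | Change | Follow-up only | Covariate |
|---|---|---|---|
| 105 (complete data) | SE 0.376, 76% | SE 0.317, 88% | SE 0.303, 91% |
| 73 (105 × 0.7 = 73.5) | SE 0.450, 60% | SE 0.381, 75% | SE 0.363, 79% |

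**Dropout.** The 73-per-group row uses completers only. A mixed model also keeps the dropouts' baselines. In 4,000 simulated trials starting from 105 per group with 30% dropout, the interaction had SE 0.420 against 0.357 for covariate adjustment. The loss is 1 − (0.357/0.420)² ≈ 28%, and the variance is about 1.27 times that of follow-up scores alone. Power for the interaction is then Φ(1/0.420 − 1.96) = Φ(0.42), about 66% rather than 60%.

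**The case against.** The strongest reply is that the section never says baseline is an outcome level, that the interaction coefficient is the effect, or that change scores are compared. It names only the two follow-ups as time-points and straight afterwards promises baseline adjustment. Read that way, the plan intends follow-up outcomes adjusted for baseline, and the loss is zero. This stands in part: the intended model may be the efficient one. But the listed terms do not fit that model, so the wording needs correcting under either reading.

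Second, even with baseline in the outcome vector, the group difference at a follow-up can be reported as group term plus interaction. With complete data that contrast has variance 1.00σ², not 1.40σ². This stands. The 35% applies only if the interaction coefficient itself is reported, and the article does not say.

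Third, an article may leave the form of adjustment to a fuller document. That would answer a complaint about missing detail. Here, however, the article does fix the model terms, and their most natural reading is the inefficient one.

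A reader might also infer that the plan misses its 80% target because the change contrast has only 64% power at 80 per group. The documents do not support that test: 80 is the figure before corrections for dropout, clustering and repeated measurements. At about 73 per group even the covariate-adjusted analysis reaches only 79%, so that shortfall is not due to the change contrast alone.

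**Conclusion.** The point holds in conditional form, with moderate severity. The stated terms, read with the three repeated measurements in the sample size section, most naturally put baseline pain in the outcome vector, and the adjustment sentence does not remove it. If the effect is read from group × time, the loss against baseline as a covariate is about 35% with complete data at r = 0.30 and about 28% with 30% dropout. With complete data it would be 25% at r = 0.5 and 15% at r = 0.7. Power at 105 per group with complete data falls from about 91% to 76%.

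It would go too far to say that the plan certainly compares change scores, or that its results would be biased. The reported contrast is not named, and among participants randomised in the same step each of these estimators targets the same difference. What is at risk is precision. Adoption and satisfaction, which are among the primary implementation outcomes, are not affected.

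The figures assume equal variances over time, a correlation of 0.30 between baseline and each follow-up, two-sided 5%, no multiplicity adjustment, and no contribution from clustering.

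**What to change.** In the Quantitative data analysis section:
- State that 10-week and 6-month pain are the outcomes, and that baseline pain and its interaction with time are prespecified covariates for every participant, whatever imbalance is observed.
- Alternatively, keep all three measurements and constrain baseline means to be equal across groups within each randomisation step. The restriction to steps is needed because participants who cannot read or write Portuguese are randomised to two of the three groups only.
- Name the between-group contrast reported at 10 weeks and at 6 months.
- Apply the same model to the secondary continuous outcomes.

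This takes a few sentences and needs no new data and no change to the sample size. If the covariate model was always intended, it only brings the listed terms into line with that intention.
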